## Sample size and recruitment

### Sample size calculation

This is an observational study designed to inform potential future studies. Recruitment will be pragmatic and designed to maximise participant numbers, without a pre-determined sample size from within a limited pool.

There are currently insufficient studies to provide data for power calculations. This study will provide pilot data to help inform whether further studies are warranted and provide data to power future studies.

### Planned recruitment rate

***‘Mama’ sub-study***

The aim of recruitment will be to maximise number of participants in the study. Approximately 15 women complete a pregnancy (give birth to a live infant) a year at the Royal Brompton Hospital CF Maternal Health Service, and patient involvement workshops indicate approximately two-thirds would be inclined to enrol in the trial. Due to the follow up duration we would expect to be able to recruit 20-25 participants.

Participants will be eligible to enrol at any stage in their pregnancy and will be consented for retrospective access to clinical data collected prior to enrolment that is included in the study.

*‘****Mini’ sub-study***

Mirroring the Mama sub-study, with most infants expected to be enrolled via this route, this will provide an overall pool of 15 babies per year. With two-thirds expected to enrol this will lead to around 10 infants per year. Children already born and under the age of 12 months at first visit can also be included which will add an estimated five further infants to the study. Overall, the expected recruitment over 3-year period will be 25 – 35 infants.

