***Sub-study 1 – ‘Mama’ (pre-conception, pregnancy and parenthood)***

‘Mama’ is a sub-study of pre-conception, pregnancy and parenthood in adult females with CF. This is a prospective, mixed-methods, observational cohort study, collecting data generated in a clinical setting.

Participants will be recruited from the Royal Brompton Hospital (RBH) CF Reproductive and Maternal Health Service, up to 12 months prior to their having confirmed a planned date for actively trying to conceive, with follow-up until two years post-partum.

There will be up to a maximum of eight in-person study visits. These will occur:

- once up to 12 months pre-conception,
- once per trimester of pregnancy (X3), and
- at defined intervals post-partum.

All in-person visits will involve blood tests, lower respiratory tract samples, urine samples, lung function, health and quality of life questionnaires, in addition to taking biological samples for CFTRm assay (blood and breastmilk) and sweat chloride measurements.

The pre-conception, third trimester and 12-month post-partum in-person study visits will include radiological imaging which involves a paired synchronous lung CT and MRI when not pregnant or breastfeeding (or only MRI if visit occurs during pregnancy/lactation). In the third trimester this will also encompass a fetal MRI.

Standardised oral glucose tolerance tests will occur in the second and third trimester visits if clinically indicated (standard of care).

Semi-structured video interviews will be recorded for thematic analysis and will occur:

- once during pre-conception
- once ante-partum, and
- once post-partum.

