# Eligibility criteria

## Inclusion criteria

***Inclusion criteria – ‘Mama’ sub-study:***

- Written informed consent obtained from participant.
- Under the care of Royal Brompton Hospital CF Reproductive and Maternal Health Service
- Age 16 years or above at time of recruitment.
- Confirmed diagnosis of CF.
- Planning a pregnancy or pregnant at time of recruitment.
- Ability to adhere to the required visits and investigations.

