# Recruitment process

Participant recruitment will only commence once the study team has ensured that the following approval/essential documents are in place:

1. The main REC, and Health Research Authority (HRA) approval.

2. Final sponsorship and/or confirmation of Capacity and Capability (C&C).

3. Sponsor has conducted the trial initiation procedure.

4. Signed delegation of Duties and Signature Log is completed.

All subjects who wish to enter the study will be screened and consented by the Chief Investigator, or one of the qualified clinicians involved in the study as Clinical Co-investigator.

All pregnant females with CF who are looked after by the Royal Brompton Hospital (RBH) will be approached to assess suitability based on medical notes and interest in taking part in the study. The CI leads the RBH CF Reproductive and Maternal Health Service where potential participants will be identified and provided with study information verbally. After this discussion they will receive a Patient Information Sheet (PIS).

Infants will be identified through the above service, either from mothers who are already pregnant when recruitment opens or those who become pregnant and are expected to deliver within the study timeframes. Parents of infants recently born and below 12 months of age will also be approached. It is anticipated that many of the infants will be born to mothers enrolled in the ‘Mama’ sub-study, but this is not an inclusion criterion. Those infants whose biological father is a person with CF under the care of the RBH Adult CF Service will be identified through the general CF clinics, and fathers given the same PIS.

After the infant is born inclusion/exclusion criteria will be assessed by a paediatrician via phone or video call and if eligibility is met they will be consented to enter the study..

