## Endpoints

### Primary endpoints

As an observational study, a combination of multiple endpoints will be monitored to identify areas of interest that may warrant and benefit from future investigation in larger studies.

Below are the endpoints which will be explored based on the currently available literature and research in the field.

*‘Mama’ sub-study*

1. Change in percent predicted FEV_1_ (ppFEV_1_) from pre-conception/baseline to end of pregnancy, and at 12- and 24-months post-partum.
2. Incidence of CF-related pulmonary complications during pregnancy.
3. Incidence of premature delivery (defined as birth <37 weeks gestation).

*Combined ‘Mini’ and ‘Midi’ sub-study*

1. The number of participants with:
2. Liver dysfunction (ALT/AST/GGT/bilirubin above upper limit of normal). This is prospectively obtained in the ‘Mini’ sub-study, and retrospectively reviewed from medical records in the ‘Midi’ sub-study.
3. Presence of congenital abnormalities including cataracts (based on medical history and examination)
4. The number of participants with normal IRT subsequently diagnosed with CF (based on a combination of CF genetic tests, sweat chloride, and faecal elastase where appropriate)
5. The number of participants with an abnormal lung clearance index (LCI) (‘Midi’ only)

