### Primary endpoint analysis

A descriptive analysis of the endpoints will be completed. For categorical variables (e.g. presence of cataracts) they will be summarised as frequencies (%). For continuous variables (e.g. weight centiles) they will be reported as a mean (standard deviation) or median (inter-quartile ranges) dependent on sample distribution.

For comparisons across CFTRm exposed and non-exposed groups, a chi-square or Fisher’s exact test will be used for categorical variables, and a two-sample t-test or Mann-Whitney U test for continuous variables. Confounders including but not limited to cumulative time of exposure to CFTRm, maternal health, and gestation of offspring will be considered.

In the ‘Mini’ sub-study, enrolling offspring for their first visit up to the age of 12 months allows for maximising sample size although resulting in the possibility of missing early life events. A sensitivity analysis to test assumptions such as only including those up to six months of age will be undertaken.

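### Open entry through pregnancy, with none after delivery, can bias the 'Mama' premature delivery incidence downwards when it is summarised as a simple frequency

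*Protocol*

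**What the plan says.** All references are to the protocol; no SAP is at hand.

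- **Eligibility (section 7.1, 'Mama').** The woman must be "Planning a pregnancy or pregnant at time of recruitment". No section admits a woman to 'Mama' after she has delivered.
- **Entry time.** Section 6.1 opens recruitment "up to 12 months prior to their having confirmed a planned date for actively trying to conceive". Section 15.3.2 adds "Participants will be eligible to enrol at any stage in their pregnancy". Section 8 states that "All pregnant females with CF who are looked after by the Royal Brompton Hospital (RBH) will be approached".
- **Endpoint (section 15.2.1).** One of the three primary 'Mama' endpoints is "Incidence of premature delivery (defined as birth <37 weeks gestation".
- **Analysis (section 15.4.2).** For categorical variables, "they will be summarised as frequencies" with percentages. Nothing there conditions the 'Mama' denominator on gestation at entry. The only analysis that addresses late entry is a sensitivity analysis on age at first visit in 'Mini'.
- **Retrospective data (section 15.3.2).** Women who enrol "will be consented for retrospective access to clinical data collected prior to enrolment that is included in the study". This covers enrolled women only.
- **Size (section 15.3.2).** About 15 live births a year, about two-thirds willing, 20-25 participants expected.

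**The concern.** This is left truncation. A woman enters the cohort only if she is approached before she delivers. If she delivers at 30 weeks before consent, the outcome itself shuts her out. A woman consented at 34 weeks cannot have delivered before 34 weeks, and one consented at 37 weeks or later cannot have the event at all, yet both count fully in the denominator. Retrospective access to records does not help, because the missing women were never enrolled.

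Section 4.1 asks whether the older finding of a higher pre-term risk still holds in the modulator era, and section 15.3.1 intends the data to inform and power later studies. An error from this source runs towards apparent improvement. It is also not visible in a confidence interval and does not shrink when data are pooled.

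**Working it through.** **The plan's own figure.** 15 births a year × 2/3 = 10 a year, so 20-25 women corresponds to 2 to 2.5 recruiting years. The protocol does not state that window, so the figure is compatible rather than strictly reproduced. The protocol gives no expected preterm rate.

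**Formula.** Let p be the true preterm risk. Let a and b be the probabilities that a woman is enrolled before delivery, given a preterm and a term delivery. The simple frequency then estimates

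naive = p·a / [p·a + (1 − p)·b].

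If entry time is unrelated to delivery time, a later delivery leaves more time to be enrolled. So a ≤ b and naive ≤ p, with equality when everyone enters before any delivery can occur.

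**Assumptions (not in the protocol).** p = 20%; term births uniform over 37-41.5 weeks (mean 39.25); preterm births either uniform over 26-37 weeks (mean 31.5) or clustered close to 37 weeks. The uniform shape can be worked by hand.

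**All enter uniformly over 6-41.5 weeks (35.5 weeks wide).**
- a = (31.5 − 6)/35.5 = 0.718, so 28% of preterm deliveries are missed.
- b = (39.25 − 6)/35.5 = 0.937.
- naive = 0.2 × 0.718 / (0.2 × 0.718 + 0.8 × 0.937) = 0.1437/0.8930 = 16.1%.

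Simulation gives 16.1-17.5% across the two preterm shapes. With entry uniform over 0-40 weeks it gives 16.8-18.1%.

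**30% enter that way, 70% enter early.**
- a = 0.7 + 0.3 × 0.718 = 0.915; b = 0.7 + 0.3 × 0.937 = 0.981.
- naive = 0.2 × 0.915 / (0.2 × 0.915 + 0.8 × 0.981) = 18.9%.

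Simulation gives 18.9-19.3% across the two shapes.

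A share near 30% is plausible if the late entrants are mainly women already pregnant when recruitment opens: 15 × 35.5/52 × 2/3 ≈ 6.8 women, or 27% of 25 and 34% of 20.

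**Other entry patterns, true 20% (simulated).**

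| Entry pattern | Reported incidence |
| --- | --- |
| All by 12 weeks | 20.0% |
| 30% uniform over 12-40 weeks, rest early | 18.7-19.2% |
| Half at 28-40 weeks, rest early | 14.6-16.8% |
| All at 28-40 weeks | 7.7-13.0% |

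With all entering uniformly over 0-40 weeks, a true 10% becomes 8.2-9.0% and a true 30% becomes 25.7-27.5%.

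**Against sampling error.** With 25 women and a true 20%, 5 events are expected. The shortfall is 25 × (0.20 − 0.189) ≈ 0.3 events in the mixed case and 25 × (0.20 − 0.161) ≈ 1 event when all enter uniformly. The exact 95% interval for 5/25 is 6.8% to 40.7%.

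**Possible repairs.**
- Dropping only entrants at or after 37+0 weeks: b becomes (37 − 6)/35.5 = 0.873, and naive = 0.1437/(0.1437 + 0.8 × 0.873) = 17.1%. Simulation gives 17.1-18.5% across the shapes. Bias remains because the early preterm deliveries are still missing.
- Restricting to entry before 24 weeks returned 10%, 20% and 30% for those true rates in every scenario that had such women. No delivery before 24 weeks was assumed.
- A delayed-entry estimate on the gestational-age scale returned the true rates to within 0.1 percentage point.

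**The case against.** The strongest reply is that the normal route into 'Mama' is early. Recruitment starts before conception, Table 1 places consent in the pre-conception column, and the women come from a service that already follows them. Late entry may be confined to those pregnant at opening. The bias is then about one percentage point, or a fraction of one woman, inside an interval more than 30 points wide. Open entry is also a deliberate trade to gain numbers from a limited pool; the objective is to record outcomes; no test against a historical rate is planned; and a SAP is promised that could define the denominator. All of this stands as to size. It does not remove the mechanism: the entry rule and the plain frequency are both set in the protocol, and late entry is addressed for 'Mini' but not for 'Mama'.

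Three stronger readings are tempting, and the protocol does not support them.

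- **That the incidence is certainly, or substantially, biased.** The distribution of gestation at entry is not fixed, and the bias is nil if all enter early.
- **That section 8 itself shows late entry to 'Mama'.** Its phrase "either from mothers who are already pregnant when recruitment opens or those who become pregnant" describes how infants are identified for 'Mini'. Late entry to 'Mama' rests on sections 7.1 and 15.3.2.
- **That a different prematurity rate in 'Mini' would expose the bias.** 'Mini' also takes infants of fathers with CF and of mothers outside 'Mama', and excludes some infants for comorbidity, so its rate may differ anyway. It is a partial safeguard, since an infant born preterm before maternal consent can still enter there.

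**Conclusion.** The point holds as a possible downward bias in one primary endpoint. As written, entry at any gestation, no entry after delivery and a simple frequency together mean that late enrolment can lower the reported incidence of premature delivery and cannot raise it. For a true 20%, expect about 19% if some 30% enter uniformly through pregnancy and the rest early, about 16 to 17.5% if all enter uniformly, and no bias if all enter early. These figures rest on assumed delivery and entry distributions, and on entry time being unrelated to delivery time. With 20-25 women, sampling error will usually exceed the bias, so a reader should not infer that the study is bound to show a false improvement. The change is still worth making, because it uses data already held and removes an error that the interval does not show.

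**What to change.** In sections 15.2.1 and 15.4.2:

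1. Base the primary estimate of premature delivery on women enrolled pre-conception or before a fixed early gestation, for example 24+0 weeks. Alternatively, use a delayed-entry estimate on the gestational-age scale, with each woman at risk from her gestation at enrolment, provided the early risk sets are not too thin. In a cohort this small, restriction may be the more stable choice.
2. Report the distribution of gestation at enrolment.
3. Give the frequency among all enrolled women as secondary.
4. Do not rely on excluding only entrants at or after 37+0 weeks, which leaves most of the bias.

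The cost is a few sentences. Gestation at enrolment follows from the consent date, the birth date and gestation at birth, which the endpoint needs anyway. The downside is a somewhat smaller denominator or a wider interval for this one endpoint. Eligibility, visits and recruitment are unchanged.

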***‘Midi’ sub-study***

There is an existing cohort of around 30 infants born to a parent with CF aged 3 – 6. Anticipating around a third of these will enrol to the study should lead to around 10 participants in the first year of the study.

Infants newly turning three during the duration of the trial will amount to around 15 / year. Continuing with a one-third recruitment rate this will lead to another 10 over the following two years, leading to an estimated total of 20.

A lower enrolment rate is anticipated within the ‘Midi’ sub-study due to the loss of the joint maternal/infant enrolment within ‘Mama’ and ‘Mini’, as well as the investigations within this sub-study all being additional to clinical care.

## Statistical analysis plan

### Summary of baseline data and flow of patients

Recruitment is pragmatic with an aim to maximise participation from within a limited group. Baseline data and flow of patients will be provided at the final study report.

### Primary endpoint analysis

A descriptive analysis of the endpoints will be completed. For categorical variables (e.g. presence of cataracts) they will be summarised as frequencies (%). For continuous variables (e.g. weight centiles) they will be reported as a mean (standard deviation) or median (inter-quartile ranges) dependent on sample distribution.

For comparisons across CFTRm exposed and non-exposed groups, a chi-square or Fisher’s exact test will be used for categorical variables, and a two-sample t-test or Mann-Whitney U test for continuous variables. Confounders including but not limited to cumulative time of exposure to CFTRm, maternal health, and gestation of offspring will be considered.

In the ‘Mini’ sub-study, enrolling offspring for their first visit up to the age of 12 months allows for maximising sample size although resulting in the possibility of missing early life events. A sensitivity analysis to test assumptions such as only including those up to six months of age will be undertaken.

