# Introduction

## Background

Almost all studies on the outcomes of pregnancy in females with cystic fibrosis (CF) were limited by small sample sizes and occurred prior to the widespread availability of CFTRm. Females with CF were found to have poorer outcomes, with a higher risk of pre-term birth, gestational diabetes and congenital abnormalities (1). Updated studies are now required to review if these prior conclusions are still valid given the increased health stability and improved survival conveyed by modulator therapy. Since the widespread introduction of CFTRm, there has been an associated dramatic increase in the number of pregnancies amongst females with CF (2,3), making this study important and timely.

Consistent with most novel drug therapies, females who were pregnant or actively trying to conceive were excluded from CFTRm clinical trials, meaning that all data on these medications during pregnancy has been gathered from retrospective reviews and case studies. Without robust evidence, decisions around continuing or ceasing CFTRm prior to or during pregnancy are challenging, particularly as CFTRm remain unlicensed for use in pregnancy. Despite this approximately 90% of females with CF elect to continue CFTRm during pregnancy (4). There have been reports of health decline in females with CF who have stopped CFTRm therapy during pregnancy (5), however this must be weighed against the potential for, as yet unknown consequences to the developing fetus.

Data from animal models has shown that all components of CFTRm drugs (most commonly used: elexacaftor, ivacaftor and tezacaftor (ETI) (6)) cross the placenta and thus result in a degree of fetal exposure. Although no specific therapeutic drug monitoring is available, studies did show that ETI levels have been found to be comparable in maternal, cord and infant blood, suggesting a therapeutic concentration(7). Low levels of ETI were also found in breastmilk.

Due to the rapidly changing landscape of CF health, there are no consensus guidelines currently for what, if any, clinical follow up or investigations those children born to females with CF should have. Suggestions from limited data concentrate on ophthalmological reviews for potential cataracts, and regular liver function testing in infants with continued drug exposure via breast feeding (7), but these are yet to become standardised or adopted into common practice.

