***Exclusion criteria – ‘Mini’ sub-study:***

- Legal guardians’ inability to provide consent to participate in the study.
- Mother of infant has significant comorbidities unrelated to CF which could affect infant outcomes based on investigator discretion.
- A significant comorbidity in the infant unrelated to CFTR modulator exposure which could affect their outcomes, based on investigator discretion.

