The RBH CF Reproductive and Maternal Health Service have a database of children born to people with CF under their care. This database will allow the study team to locate children who are or will be between three to six years for inclusion in the ‘Midi’ sub-study. Parents of these children will preferably be contacted during their routine clinic visits, with follow up information sent via email and/or phone calls. If there are no scheduled clinic visits upcoming, they will be approached via phone. Furthermore, offspring enrolled in the ‘Mini’ sub-study can also take part in the ‘Midi’ sub-study as/when they reach the appropriate age within the study period.

Should parents be interested in the study, they will receive a PIS for which they will have at least 24 hours to consider whether they want their child enrolled in the study.

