# Statistical design

## Statistical input in study design

All three sub-studies described in this protocol are observational in design. Descriptive analyses will be used to report the data. Within this context no complex statistical analyses are anticipated which require statistician input in the design phase and a statistical analysis plan will be written prior to final analysis.

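### The combined 'Mini' and 'Midi' endpoints are compared by CFTRm exposure without separating the sub-studies, so a sub-study difference in case-finding or eligibility can appear as an exposure effect

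*Protocol*

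**What the plan says.** Section 15.2.1 lists liver dysfunction, congenital abnormalities and CF diagnosed after a normal IRT under one label, "Combined ‘Mini’ and ‘Midi’ sub-study". Section 15.2.2 does the same for birth outcomes, blood pressure, growth and development. Lung clearance index and lung MRI are marked for 'Midi' only, and cranial ultrasound and the CFTRm assay for 'Mini' only.

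The analysis in 15.4.2 is "For comparisons across CFTRm exposed and non-exposed groups, a chi-square or Fisher’s exact test will be used for categorical variables", and 15.4.3 carries it over to the exploratory endpoints. Neither section mentions sub-study. On adjustment, 15.4.2 says only: "Confounders including but not limited to cumulative time of exposure to CFTRm, maternal health, and gestation of offspring will be considered".

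The two samples differ on the protocol's own text:

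- **Source of liver data (15.2.1):** "This is prospectively obtained in the ‘Mini’ sub-study, and retrospectively reviewed from medical records in the ‘Midi’ sub-study". Table 3 schedules no liver test and no eye review for 'Midi'.
- **Visits (synopsis, 6.1):** up to four in 'Mini', at most two in 'Midi'.
- **Exclusions (7.2):** 'Mini' excludes on "Mother of infant has significant comorbidities unrelated to CF which could affect infant outcomes based on investigator discretion", and also on significant infant comorbidity unrelated to CFTRm. 'Midi' has no maternal criterion and excludes only conditions known to affect lung function or imaging.
- **Overlap (section 8):** "offspring enrolled in the ‘Mini’ sub-study can also take part in the ‘Midi’ sub-study as/when they reach the appropriate age within the study period".

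**The concern.** A two-by-two table of exposure against outcome, pooled over both sub-studies, treats the children as one sample. If one sub-study has both a higher exposed share and a higher chance that a case is found, exposure stands in for sub-study, and the table shows a difference that CFTRm did not cause. If the frequencies run the other way, for example because the stricter 'Mini' exclusions remove cases, the same mechanism can hide a real difference.

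The study is meant to supply pilot data for powering later studies and to support guidance on following up these infants (4.3.1, 15.3.1). A false or masked safety signal would carry forward into both.

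**Working it through.** **Plan's own figures (15.3.2).** 'Mini': 15 × 2/3 = 10 a year plus 5 already born, so 10 × 2 + 5 = 25 to 10 × 3 + 5 = 35. 'Midi': 30 × 1/3 = 10, plus 15 × 1/3 × 2 = 10, total 20. Both reproduce, giving 45 to 55 child records.

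**Assumptions.** The protocol gives no exposed share for either sub-study, no outcome frequency and no significance level. I take 30 'Mini' and 20 'Midi' children, no CFTRm effect in either, 90% exposed in 'Mini', 30% to 90% exposed in 'Midi', outcome frequencies of 30% v 10% or 40% v 5% ('Mini' v 'Midi'), and a two-sided Fisher test at 0.05.

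**Formula.** With e₁, e₂ exposed and u₁, u₂ non-exposed children in 'Mini' and 'Midi', and outcome frequencies p₁, p₂:

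- exposed rate = (e₁p₁ + e₂p₂)/(e₁ + e₂)
- non-exposed rate = (u₁p₁ + u₂p₂)/(u₁ + u₂)

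**Example, 90% v 30% exposed, outcome 30% v 10%.** Exposed: (27 × 0.30 + 6 × 0.10)/33 = 8.7/33 = 0.264. Non-exposed: (3 × 0.30 + 14 × 0.10)/17 = 2.3/17 = 0.135. Odds ratio = (0.264/0.736)/(0.135/0.865) = 2.3.

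| Exposed share, 'Mini' v 'Midi' | Exposed / non-exposed | Odds ratio, outcome 30% v 10% | Odds ratio, outcome 40% v 5% | Fisher test significant (same two columns) |
|---|---|---|---|---|
| 90% v 90% | 45 / 5 | 1.0 | 1.0 | 1.8%, 1.0% |
| 90% v 70% | 41 / 9 | 1.5 | 1.9 | 1.7%, 3.6% |
| 90% v 50% | 37 / 13 | 1.9 | 2.9 | 5.9%, 13.7% |
| 90% v 30% | 33 / 17 | 2.3 | 4.0 | 10.9%, 30.1% |

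If the outcome frequency is the same in both sub-studies (30% v 30%), the odds ratio is 1.0 in every row. Comparing within sub-study gives 1.0 throughout, by construction.

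**Overlap.** A child of age *a* months at study month *t* reaches 36 months of age within a 36-month study only if 36 − a + t ≤ 36, that is a ≥ t. Only children born by study opening qualify: the roughly 5 already-born infants at most, or about 2 at one-third uptake (5 × 1/3).

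**What stratification leaves untouched.** In Table 2, liver tests at visits 3 and 4 are only for breastfed infants recently exposed to CFTRm, and eye review is recorded only for exposed children. If each liver test has a 10% chance of a value above the upper limit, two tests give 1 − 0.9² = 19% ever abnormal and four give 1 − 0.9⁴ = 34%. At 5% per test the figures are 10% v 19%, and at 20% they are 36% v 59%. The three-monthly clinical tests for exposed infants (9.4.6) add to this where abnormal results lead to further recorded testing.

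**The case against.** The strongest reply is that this is analysis-plan detail. Section 15.1 says "a statistical analysis plan will be written prior to final analysis", the confounder list in 15.4.2 is open-ended, and the combined label heads a list of endpoints rather than ordering an unadjusted pool. It stands that the later plan could stratify. But 15.4.2 already names the test for endpoints already defined as combined, and its confounder sentence gives no method and does not name sub-study, age or number of examinations. That is a stated choice which can be improved, not an omission.

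Three stronger readings are tempting, and the documents do not support them:

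- **That the exposed share is known to differ.** Section 4.1 reports that "approximately 90% of females with CF elect to continue CFTRm during pregnancy", but that concerns mothers with CF. It is not a 'Mini' share, since children of fathers with CF are also eligible. A lower share in 'Midi' is plausible because it draws on earlier births, but it remains an assumption.
- **That every combined endpoint is distorted by visit number.** Gestation, birth weight, unit admission and the IRT result are collected once, in the same way, for all participants (9.4.2). Only eligibility and birth era can affect them.
- **That double counting is a material problem.** Endpoints count participants, unique IDs are used (13.1), and the overlap is about 2 to 5 children.

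**Conclusion.** The point holds as a possibility that the stated method does not guard against, not as a demonstrated bias. Bias needs both a different exposed share and a different outcome frequency; if either is equal there is none. When both differ, the spurious odds ratio under the assumptions above runs from about 1.5 to 4.0. At the milder split (90% v 70%) the Fisher test is rarely significant, so the harm lies in the reported rates and estimate rather than in false significance.

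Liver dysfunction is the endpoint with a documented difference in ascertainment. Blood pressure, growth and development are exposed to the difference in visits. Endpoints confined to one sub-study are unaffected. Because testing inside 'Mini' itself depends on exposure, stratifying by sub-study is necessary but not sufficient.

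**What to change.** In section 15.4.2, applying also to 15.4.3:

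1. Report each combined endpoint by sub-study first.
2. Give any combined exposed v non-exposed contrast as an estimate stratified by sub-study with a 95% CI (Mantel-Haenszel, or exact stratified where counts are sparse).
3. Count each child once, by linking 'Mini' and 'Midi' records under one ID.
4. Use as denominator only children with a result for that endpoint.
5. Limit the exposure contrast to examinations scheduled in both exposure groups. For liver function this means 'Mini' visits 1 and 2, with later 'Mini' tests and 'Midi' record data described only. Lens findings from the exposed-only eye review are likewise described, not compared.
6. Show one child per family as a sensitivity analysis, since siblings and twins are not independent.

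The cost is a few sentences and an ID link, slightly wider intervals, and fewer liver results in the contrast. No visit or test changes.
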